### **8.3 Lost to follow-up**

Subjects who stop scheduled study follow-up, fail to complete prescribed study procedures, or cannot be contacted by the investigator may be considered lost to follow-up. Notify subjects in time window in advance to reduce lost follow-up and missing data.

Each subject should leave a detailed contact address, telephone number, ID card and other information, and the doctor should leave his or her contact number with the subject, so that the subject can seek the doctor's help when the condition changes, which is also conducive to the doctor to keep abreast of the condition changes, remind the subject to return visit in time, and avoid the loss of visit.

## **9 Evaluation of study outcomes**

### **9.1 Primary and secondary efficacy evaluation indicators**

### **9.2 Safety evaluation indicators**

- (1) physical examination: vital signs, Respiration, heart rate, blood pressure
- (2) Severe arm pain, compartment syndrome
- (3) Skin Adverse Reactions: erythema, itching, vesicles, exudation, pigmentation changes, desquamation, etc., at the local site
- (4) Any adverse reactions that may occur during the trial and abnormal changes in related test parameters
- (5) Adverse Events

### **9.3 Adverse Events and Serious Adverse Events**

#### **9.3.1 Adverse Event (AE) Definition**

Adverse Events: The term "adverse events" encompasses the occurrence or worsening of any signs, symptoms, syndromes, or diseases that affect the health of subjects during the observation period of a clinical study. This term also includes clinically relevant situations discovered during laboratory or other diagnostic procedures, such as the need for unplanned medical intervention, withdrawal from the study, or abnormal laboratory test results. Adverse events may be: new diseases; worsening of symptoms, signs, or conditions related to the treatment; worsening of comorbidities; effects of control drugs; unrelated to participation in the study; or a combination of one or more factors. Therefore, the term "adverse events" does not necessarily imply a causal relationship with the study drug.

#### **9.3.2 Serious Adverse Event (SAE) Definition**

Serious Adverse Event (SAE): Refers to the following adverse events that occur at any dose of the investigational drug or at any time during the observation period, including death or life-threatening events, hospitalization or prolonged hospitalization, permanent disability, teratogenic effects, induction of cancer, events of significant medical importance (meaning those that do not immediately jeopardize life or lead to death or require hospitalization but may harm the patient or require measures to prevent one of the consequences defined above), necessitating medical intervention to prevent permanent damage or harm.

#### **9.3.3 Adverse Event Reporting**

All AEs (whether related to the experimental intervention or not) must be fully documented from the time the informed consent form is signed until the end of the study.

### **9.3.4 Serious Adverse Event Reporting**

For all serious adverse events occurring during a clinical study, whether reported for the first time or as a follow-up, the investigator must immediately complete and sign and date a Serious Adverse Event Report Form and report it immediately (no later than 24 hours after the SAE is known) to the The applicant, the ethics Committee and the group leader, and written report to the local provincial drug supervision and administration department, Health Bureau adverse event detection event center. The investigator should ensure that all required information is submitted within the above time frame.

In general, a sufficiently detailed description of the adverse event should be included to allow for a thorough medical evaluation of the case and an independent assessment of the likelihood of causality. In addition, the investigator must provide information on other possible causes of the adverse event, such as combined medications and comorbidities. In the event of a subject's death, the investigator must submit a summary of autopsy results (if available) to the professional organization for adverse drug reaction monitoring of the province, autonomous region or municipality directly under the Central Government as soon as possible. contact information for SAE reporting is detailed in the investigator's file provided to each center. The original SAE report form must be kept in a safe place by the center.

## **10 Statistical Analysis**

### **10.1 General Method**

During statistical analysis, the following steps will be taken: first, an examination of the number of completed cases and dropout status of the patients; then, an analysis of the baseline characteristics related to demographics for the two groups at the time of patient inclusion, assessing comparability between the study group and the control group; efficacy evaluation will involve determining efficacy indicators and comparing the efficacy between the two groups; safety evaluation will include a comparison of laboratory indicators and clinical adverse reactions.

All statistical tests will be two-tailed, and a p-value less than or equal to 0.05 will be considered statistically significant for the tested differences.

Data analysis was consistent with the principle intention-to-treat (ITT) of per-protocol (PP). For quantitative variables, descriptive statistics will include means, standard deviations, medians, minimum values, maximum values, lower quartiles (Q1), upper quartiles (Q3), and for categorical variables, the description will include counts and percentages for each category.

Comparisons between the two groups for general characteristics will be analyzed using appropriate methods based on the type of indicator. The comparison between the two groups used Student's t-test or the Mann-Whitney U-test for continuous variables, and chi-square test or Fisher's exact test for categorical variables. For repeatedly measured data, we used a linear mixture model for statistical analysis, with participants as random effects, time and group as fixed effects, multiple comparisons of data were correction by Bonferroni. Complications were analyzed by calculating the risk ratios and 95% confidence interval.

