## **7.4 Follow-up and Adherence**

The observation period was 3 months, and participants were evaluated clinically at 3 days, 7 days, 2 weeks, 6 weeks, and 12 weeks after initiation of treatment, with X-ray evaluation at 2 weeks, 6 weeks, and 12 weeks.

The researchers should carefully implement informed consent so that the subjects fully understand the test requirements and cooperate with the researchers. The surgeon treated the participants free of charge and directed rehabilitation training

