### 7.6 Research Flow Chart

|                                                 | Screening Period | Treating Period |      |       |       | Follow-up Period |
|-------------------------------------------------|------------------|-----------------|------|-------|-------|------------------|
| Time                                            | Day0             | Day3            | Day7 | Week2 | Week6 | Week12           |
| Basic information                        |                  |                 |      |       |       |                  |
| Informed Consent Form                           | √                |                 |      |       |       |                  |
| Medical history, past medical history           | √                |                 |      |       |       |                  |
| Inclusion/exclusion criteria                    | √                |                 |      |       |       |                  |
| Subjects were randomized                        | √                |                 |      |       |       |                  |
| General evaluation and safety evaluation |                  |                 |      |       |       |                  |
| visual analogue scale (VAS) scores              | √                | √               | √    | √     | √     | √                |
| Grading of swelling degree                      | √                | √               | √    | √     | √     | √                |
| radiographic parameters                         | √                |                 |      | √     | √     | √                |
| Gartland-Werley (G-W) wrist scores              |                  |                 |      |       | √     | √                |
| Adverse Event Reporting                         |                  | √               | √    | √     | √     | √                |
| Summary of research completion                  |                  |                 |      |       |       | √                |
| Drug combination                                |                  | √               | √    | √     | √     | √                |
| Other work                               |                  |                 |      |       |       |                  |
| Assign random numbers                           | √                |                 |      |       |       |                  |

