### **10.2 Analysis of primary and secondary study endpoints**

Analysis of primary study endpoints:

Gartland-Werley (G-W) score: The comparison between the two groups used Student's t-test or the Mann-Whitney U-test for continuous variables, and chi-square test or Fisher's exact test for categorical variables.

Analysis of secondary study endpoints:

Radiographic parameters: mixed linear model to test for differences between groups (participants as random effects, time and group as fixed effects).

visual analogue scale (VAS) score, swelling degree grade: mixed linear model to test for differences between groups (participants as random effects, time and group as fixed effects).

Complication: chi-square test or Fisher's exact test for categorical variables, analyzed by calculating the risk ratios and 95% confidence interval.

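### Section 10.1 fixes plain Bonferroni for the repeatedly measured secondary outcomes; Holm's step-down procedure gives the same 5% familywise guarantee and never rejects less (cheap improvement)

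*Protocol*

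**What the plan says.** Protocol section 10.1 sets a common significance rule: "All statistical tests will be two-tailed, and a p-value less than or equal to 0.05 will be considered statistically significant". For repeatedly measured data it plans a linear mixed model, "with participants as random effects, time and group as fixed effects", and in the same sentence adds that "multiple comparisons of data were correction by Bonferroni".

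Section 10.2 uses that model for the secondary outcomes only. For pain and swelling the entry reads "visual analogue scale (VAS) score, swelling degree grade: mixed linear model to test for differences between groups", and radiographic parameters get the same model. The primary outcome is tested outside it: "Gartland-Werley (G-W) score: The comparison between the two groups used Student's t-test or the Mann-Whitney U-test for continuous variables", with chi-square or Fisher's exact test if it is categorical.

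On visits, section 7.4 says that "participants were evaluated clinically at 3 days, 7 days, 2 weeks, 6 weeks, and 12 weeks after initiation of treatment". Radiographs follow a shorter schedule, limited to the last three of those visits. That makes five post-baseline visits for VAS and swelling and three for radiographs. The flow chart in 7.6 also schedules the "visual analogue scale (VAS) scores" at Day 0.

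The protocol does not say which comparisons form the corrected family or how many there are. It names no group-by-time term, and it gives no effect size, SD or correlation for any secondary outcome.

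**The concern.** Plain Bonferroni holds every comparison in a family of k to 0.05/k, however many of the others have already been rejected. Holm's procedure starts at the same threshold and relaxes it after each rejection, with the same guarantee against false positives. Where a treatment difference is present at several visits, Bonferroni therefore gives up some chance of showing it at each of them, and the guaranteed familywise level is no better for it.

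What is at stake is limited to secondary outcomes. Section 4 makes the effect on pain, swelling and radiographic parameters part of the secondary purpose, so the power of these comparisons is worth having when it costs no patients.

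**Working it through.** **1. The plan's own figure, and the number per arm.** Section 5.3 gives 96% against 77%, two-sided 5%, 80% power, 1:1 allocation and 10% drop-out. With the pooled-variance formula and mean proportion 0.865:

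n per arm = [1.960 × √(2 × 0.865 × 0.135) + 0.842 × √(0.96 × 0.04 + 0.77 × 0.23)]² / 0.19² = (0.947 + 0.391)² / 0.0361 = 49.6, rounded up to 50.

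That is 100 in total, and 100 × 1.10 = 110, the stated total. The calculation concerns the G-W effective rate, which lies outside the Bonferroni sentence, so it is the same under either procedure. It supplies the 50 evaluable patients per arm used below.

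**2. Thresholds.** Bonferroni tests each p-value at 0.05/k. Holm tests the j-th smallest at 0.05/(k − j + 1) and stops at the first failure.

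| Comparisons | Bonferroni | Holm, in order |
|---|---|---|
| k = 5 | 0.010 throughout | 0.010, 0.0125, 0.0167, 0.025, 0.05 |
| k = 3 | 0.0167 throughout | 0.0167, 0.025, 0.05 |

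No Holm threshold is below 0.05/k, so Holm rejects everything that Bonferroni rejects.

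**3. Familywise error.** Let m0 of the k null hypotheses be true. When Holm first rejects a true one, at most k − m0 rejections came before it, so its p-value is at most 0.05/m0. The chance that any of m0 true nulls has so small a p-value is at most m0 × 0.05/m0 = 0.05. Nothing is assumed about correlation.

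**4. Power under an assumed family.** Assumptions, none of them in the protocol: the family is the group contrast at each post-baseline visit of one outcome; 50 per arm; equicorrelated normal test statistics. A difference of d SD gives a mean statistic of d/√(2/50) = d/0.2, which is 2.5 for d = 0.5.

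Bonferroni power per visit follows directly. For k = 5 the critical value is 2.576, and Φ(2.5 − 2.576) = 0.47. For k = 3 it is 2.394, and Φ(2.5 − 2.394) = 0.54. Holm was simulated with 400,000 replicates per scenario:

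| True differences (SD) | Correlation | Per visit, Bonferroni / Holm | All visits shown | At least one shown |
|---|---|---|---|---|
| 0.4 at all five | 0.5 | 28% / 34% | 5% / 15% | 61% / 61% |
| 0.5 at all five | 0.5 | 47% / 56% | 14% / 34% | 81% / 81% |
| 0.6 at all five | 0.5 | 66% / 76% | 32% / 57% | 93% / 93% |
| 0.5 at all three | 0.7 | 54% / 61% | 35% / 51% | 73% / 73% |
| 0.5 at one of five | 0.5 | 47% / 47% (at that visit) | not applicable | not applicable |

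For a fading effect (0.6, 0.6, 0.6, 0.3 and 0 SD, correlation 0.5), power is 66% to 67% against 70% to 71% at each of the first three visits, and 14% against 22% at Week 6.

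In the scenario of 0.5 SD at all five visits, Holm adds at least one rejection in 32% of simulated trials. With no true difference at five visits and correlation 0.5, familywise error is 4.2% for both procedures.

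**5. Day 0.** If Day 0 were counted in the VAS family, k would be 6 and the first threshold 0.05/6 = 0.0083. With 0.5 SD at the five later visits and correlation 0.5, power at each later visit would then be about 44% with Bonferroni and 51% with Holm. The protocol does not place Day 0 in the family. This shows only why the family should be stated as post-baseline.

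**The case against.** The strongest reply is that nothing here is wrong. Bonferroni is standard, prespecified and keeps the familywise error at or below 5%. That stands: this is a point of efficiency.

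The second reply is that the visit-by-visit family is not in the text. With time and group as main effects only, the group effect is a single test per outcome, and for one test the two procedures coincide. This stands as a limit on the power figures. Yet 10.1 attaches a multiple-comparison correction to the repeated-measures analysis, so some family is intended, and Holm is never worse than Bonferroni in any family.

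A reader might go further and infer that the plan will declare real differences at several visits non-significant for no gain. The documents do not support that, for three reasons.

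- Holm changes a decision only when one comparison already passes 0.05/k and another p-value falls between 0.05/k and its own Holm threshold. The chance of at least one rejection is identical, and when only one visit differs the gain is below 0.1 percentage point.
- Bonferroni offers something in return: simple simultaneous confidence intervals that match its tests. The protocol does not plan any for these outcomes, though; its only stated intervals are for complication risk ratios.
- When some nulls are true, Bonferroni's realised error can be lower. In the fading scenario it is 1.0% against 2.6% for Holm. Both are under 5%, and the guaranteed level is the same.

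Correlation between visits is no argument for either side, since neither procedure uses it.

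**Conclusion.** A cheap improvement, not an error. For whatever family the sentence in 10.1 covers, Holm's procedure keeps the guaranteed 5% familywise level and rejects at least as much. If the family is the group contrast at each post-baseline visit, a sustained difference of 0.4 to 0.6 SD over five visits gains about 6 to 10 percentage points of power per visit, and the chance of showing all five rises by about 10 to 25 points. The gain shrinks towards nil as fewer visits truly differ. These sizes rest on assumed effects, correlations and family, with 50 patients per arm taken from the sample-size calculation. Only secondary outcomes are affected.

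**What to change.** In section 10.1, replace Bonferroni by Holm's step-down procedure at two-sided 5%, applied within each outcome over the post-baseline between-group comparisons. That wording also settles that Day 0 is not in the family.

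The cost is one sentence in 10.1 and no extra patients. The downside is that Holm has no simple matching simultaneous confidence intervals. Any intervals shown beside Holm-adjusted p-values should be labelled unadjusted, because such an interval can exclude zero while the adjusted p-value is above 0.05. If matching simultaneous intervals matter more to the sponsor than power per visit, keeping Bonferroni is defensible, and the protocol should then say that those intervals will be reported.

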### **10.2 Analysis of primary and secondary study endpoints**

Analysis of primary study endpoints:

Gartland-Werley (G-W) score: The comparison between the two groups used Student's t-test or the Mann-Whitney U-test for continuous variables, and chi-square test or Fisher's exact test for categorical variables.

Analysis of secondary study endpoints:

Radiographic parameters: mixed linear model to test for differences between groups (participants as random effects, time and group as fixed effects).

visual analogue scale (VAS) score, swelling degree grade: mixed linear model to test for differences between groups (participants as random effects, time and group as fixed effects).

Complication: chi-square test or Fisher's exact test for categorical variables, analyzed by calculating the risk ratios and 95% confidence interval.

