#### 5.3 Sample size

The sample size was calculated by PASS software (NCSS, Kaysville, UT) with sample allocation ratio of 1:1 between 2 groups with reference to other studies ( $n=94$ ). The difference in G-W score effective rate between the intervention group (96%) and the control group (77%) was 19% at 3 months, with a 2-sided 5% of type I error probability, and an 80% of power, allowing drop-out rate of 10%, a total of 110 cases were finally required for enrollment.

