### 6 Research Subjects

#### 6.1 Eligibility Criteria

In order to be eligible to participate in this study, an individual must meet all of the following criteria:

1. acute distal radius fracture
2. with men or women aged 18 to 85 years old
3. patients with DRFs were classified as type A and type B fractures according to AO/OTA classification
4. fresh closed fractures that have not been combined with other parts of the fracture and have not received other treatment methods
5. fresh closed fractures that have not been combined with other parts of the fracture and have not received other treatment method
6. participants who were willing to cooperate with the doctor for voluntary follow-up

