## **6.4 Methodology of research subject assignment**

Patients were randomly assigned to the topologically optimized splint group or the cast group in 1:1 ratio. Random sequence list generated by SAS (Strategic Application Software, version 9.4; SAS Institute Inc) were sealed in opaque envelopes and distributed to each center. The envelope was opened in front of the patient in chronological order of the patient's visit.

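### The primary G-W comparison is fixed as unadjusted although AO type and age are known at Day 0: valid, but it gives up some precision and protection against a realised imbalance

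*Protocol*

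**What the plan says.** Protocol section 10.2 gives the primary analysis as "Gartland-Werley (G-W) score: The comparison between the two groups used Student's t-test or the Mann-Whitney U-test for continuous variables" and, for the categorical form, "chi-square test or Fisher's exact test for categorical variables". The categorical form is the one the trial was sized on: section 5.3 says "The difference in G-W score effective rate between the intervention group (96%) and the control group (77%) was 19% at 3 months". The section names no covariate, stratum or model for G-W, whereas it does set model terms (participant, time, group) for the radiographic, pain and swelling endpoints.

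On fracture type, section 6.1 says "patients with DRFs were classified as type A and type B fractures according to AO/OTA classification", and the same list admits ages 18 to 85. The flow chart in section 7.6 places the eligibility check at Day 0, so both facts are on record before treatment.

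On allocation, section 6.4 says "Patients were randomly assigned to the topologically optimized splint group or the cast group in 1:1 ratio", from a SAS list in sealed envelopes sent to each centre. It mentions no stratification by AO type or age. Section 10.1 announces a baseline comparison of demographic characteristics but attaches no consequence to it for the primary analysis.

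**The concern.** Extra-articular (A) and partial-articular (B) fractures in adults from 18 to 85 may well differ in wrist function at 12 weeks. If so, two cheap baseline facts could sharpen the comparison and guard it against an uneven fracture mix, and the plan uses neither. About 13 treatment failures are expected in total (49 × 0.23 + 49 × 0.04 = 13.2), so a few high-risk patients falling by chance into one arm could move the result noticeably. If that were seen at the baseline comparison, any adjustment would then be chosen with the data in view. At stake are the precision of the primary result and how it reads after an unlucky draw.

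**Working it through.** **Inputs from Protocol section 5.3.** Effective rates 0.96 and 0.77; "with a 2-sided 5% of type I error probability, and an 80% of power"; "sample allocation ratio of 1:1 between 2 groups"; "allowing drop-out rate of 10%, a total of 110 cases were finally required for enrollment".

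**Reproducing the sample size.** With the pooled rate (0.96 + 0.77)/2 = 0.865, n per arm = [1.960 √(2 × 0.865 × 0.135) + 0.842 √(0.96 × 0.04 + 0.77 × 0.23)]² / 0.19² = 49.6, so 50 per arm and 100 in total. Then 100 × 1.10 = 110, the stated figure; dividing by 0.90 instead gives 56 per arm, 112 in total. The sizing is thus for an unadjusted comparison of two proportions, consistent with the planned categorical test. With 55 per arm and 10% lost, 55 × 0.9 = 49.5, so about 49 per arm are evaluable.

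**Assumptions not in the documents.** Type B share 20% or 50%; odds ratio of AO type on success 1 to 10; overall rates held at 0.77 and 0.96. Example at share 50% and odds ratio 5: cast success 0.899 (A) and 0.641 (B), mean 0.770; splint 0.986 and 0.934, mean 0.960.

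**Tests compared.** The uncorrected Pearson chi-square, and the two-stratum Cochran-Mantel-Haenszel (CMH) statistic [Σ(a − E)]² / ΣV. In each AO stratum a is the number of splint successes, E = m₁s/N and V = m₁m₀s(N − s)/[N²(N − 1)], where m₁ and m₀ are the arm sizes, s the total successes and N the stratum size. Both are referred to 3.841, with 200,000 simulated trials per scenario.

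**Over all randomisations.**

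| | Unadjusted | CMH by AO type |
|---|---|---|
| Type I error, 49 per arm, common rate 0.77 | 0.050–0.051 | 0.049–0.051 |
| Power, 49 per arm, OR 1–2 | 0.85 | 0.83 |
| Power, 49 per arm, OR 3 | 0.85 | 0.84 |
| Power, 49 per arm, OR 5 | 0.85 | 0.85 |
| Power, 49 per arm, OR 10 | 0.85 | 0.86–0.88 |
| Power, 55 per arm, OR 1–10 | 0.87–0.88 | 0.87–0.91 |

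The unadjusted columns do not move with the AO effect. At a common rate of 0.865 the exact type I error of the chi-square at 49 per arm is 0.056; that is discreteness and has nothing to do with AO type.

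Most of the apparent CMH loss at odds ratio 1 comes from its N − 1 variance. Multiplying the Pearson statistic by (N − 1)/N puts the two on one scale. The scaled unadjusted test then has power of about 0.83 at 49 per arm, and CMH differs from it by about -0.3 points at odds ratio 1 and by up to about +4 points at odds ratio 10.

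**Given an imbalance that has occurred.** At 49 per arm, a gap of at least 10 percentage points in type B share, in either direction, arises in about 25% (share 20%) to 36% (share 50%) of trials. A gap of at least 20 points arises in about 2% to 5%. Given a gap of at least 10 points, the unadjusted test behaves as follows:

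| AO odds ratio | Null rejection rate | Power, gap against the splint |
|---|---|---|
| 2 | 0.052–0.056 | 0.81 |
| 3 | 0.057–0.060 | 0.78–0.79 |
| 5 | 0.063–0.073 | 0.75–0.77 |
| 10 | 0.071–0.098 | 0.69–0.74 |

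When the gap favours the splint, unadjusted power is 0.88–0.96 at odds ratios 2 to 10. In the same subsets CMH stays near 0.05 under the null and has power 0.82–0.87. At odds ratio 1 nothing shifts.

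**Continuous form.** If covariates explain a share R² of the variance of the G-W score, 80% power becomes Φ(2.802/√(1 − R²) − 1.96): 84%, 88% and 92% for R² of 10%, 20% and 30%. These R² values are assumed. The documents give no age effect, and age was not simulated.

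**The case against.** The strongest reply is that an unadjusted comparison in a randomised trial is valid and matches the way this one was sized. That stands in full. A reader might infer from the conditional table that the plan inflates the type I error or loses its planned power. The documents do not support this: chance imbalance is already part of the sampling distribution of the test, and the bad draws are offset by the good ones.

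One assumed scenario shows the offset: 50 per arm, half type B, cast failure 8% (A) and 38% (B), splint failure 1% and 7%. With 30 v 20 type B patients against the splint, unadjusted error is 9.3% and power 71%. With exact balance the error is 3.6%, and with 30 v 20 in the splint's favour the power is 95%. Over all draws it comes to 5.1% and 85.1%. A gap of 10 or more patients occurs in 5.7% of such trials, and in 2.9% against the splint.

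Three further replies carry some weight.

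- The size depends on an AO effect that the documents do not give; the scenario above implies an odds ratio of about 7, which is strong.
- Section 6.4 is silent on stratification and does not deny it, so no stated design factor is being ignored.
- Covariates are often left to the SAP. Here, however, section 10.2 names the tests, so the point concerns a stated method and not an absent detail.

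The objection that adjustment costs power is only slightly right: on an equal scale the loss is about 0.3 points when AO type is not prognostic.

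**Conclusion.** The point holds as an optional improvement. Section 10.2 fixes an unadjusted primary comparison while two baseline facts known for every patient go unused. The test is valid and the plan's error rate is not shifted. The plan gives up some precision, and one realised result could mislead if a sizeable AO imbalance occurs and AO type is strongly prognostic.

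The effect on overall power at 49 to 55 per arm is about -0.3 to +4 points on an equal scale, or about -2 to +4 against the uncorrected Pearson chi-square. Both ranges rest on assumed type B shares of 20% or 50% and AO odds ratios from 1 to 10. The benefit for age is not quantified.

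For proportion, the open choice in the same section between chi-square and Fisher's exact test matters more: exact power at 49 per arm is 0.85 against 0.72. That is a separate matter.

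**What to change.** In section 10.2, or in the SAP before any unblinded data are seen:

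- Analyse the week-12 G-W effective rate by a Cochran-Mantel-Haenszel test stratified by AO type (A v B), and report the Mantel-Haenszel risk difference with its 95% confidence interval. Two strata are workable with about 13 expected failures, where a logistic model with several covariates would be strained.
- If the G-W score is analysed as continuous, use linear regression on group, AO type and age.
- Keep the unadjusted test as a sensitivity analysis.

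The cost is a few lines of text and code. No new data, patients or visits are needed. The one downside is the very small power loss if AO type turns out not to be prognostic.

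### For sparse two-by-two tables, chiefly complications, Boschloo's exact test would find more real differences than Fisher's at the same 5% limit (free improvement, low severity)

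*Protocol*

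**What the plan says.** Protocol section 10.1 sets the general rule for comparing categorical variables: a chi-square test or Fisher's exact test, two-tailed, where "a p-value less than or equal to 0.05 will be considered statistically significant". Section 10.2 applies the same pair to the primary Gartland-Werley comparison ("chi-square test or Fisher's exact test for categorical variables") and to safety: "Complication: chi-square test or Fisher's exact test for categorical variables, analyzed by calculating the risk ratios and 95% confidence interval". No other small-count method is named.

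Section 5.3 sizes the trial on the primary endpoint only: "The difference in G-W score effective rate between the intervention group (96%) and the control group (77%) was 19% at 3 months". The level is two-sided 5% and the planned power is 80%. The total is given as "allowing drop-out rate of 10%, a total of 110 cases were finally required for enrollment", and the arms are to be equal in size. No complication rate is assumed anywhere and no power is claimed for complications. Section 2.4.3 describes significant displacement and serious complications as clinically rare. Section 9.2 also lists local skin reactions as safety indicators, without saying how often they are expected.

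**The concern.** With about 55 patients per arm, any complication seen in fewer than ten patients overall gives an expected count below 5, and by common convention the analyst then turns to the exact test. Fisher's test conditions on the total number of events. With so few events the p-value can take only a few values, so the achieved error rate falls well short of 5%. In a safety comparison the main worry is missing a real difference, and unused error rate is power given away. An unconditional exact test uses more of the allowance without exceeding it. At stake is the chance of detecting a difference in uncommon complications.

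**Working it through.** **Inputs.** From section 5.3: 96% v 77%, two-sided 5%, 80% power, 10% drop-out, 1:1 allocation, 110 enrolled. That is 55 per arm randomized and 110 x 0.9 = 99 evaluable, so 49 or 50 per arm. Assumed here, because the protocol gives neither: the complication rates, and the convention that the exact test replaces chi-square when an expected count is below 5.

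**Step 1: the plan's own figure.** Pooled chi-square formula without continuity correction, mean rate 0.865:

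n = [1.960 x sqrt(2 x 0.865 x 0.135) + 0.8416 x sqrt(0.96 x 0.04 + 0.77 x 0.23)]^2 / 0.19^2

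= [0.947 + 0.391]^2 / 0.0361 = 49.58 per arm.

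2 x 49.58 / 0.9 = 110.2, or 99 / 0.9 = 110. The stated 110 is reproduced, and it fits the uncorrected chi-square test.

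**Step 2: error rates.** All two-by-two tables were enumerated under a common rate, and the rejection probability was maximized over that rate (sizes 49/49, 49/50, 50/49, 50/50 and 55/55).

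| Test | Maximum type I error |
|---|---|
| Fisher | 3.2-4.4% |
| Boschloo | 4.7-4.9% |
| Chi-square, uncorrected | 5.3-6.1% |

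**Step 3: where the two exact tests differ at 55 per arm.** Among sparse tables (nine or fewer events in total) they disagree on only two patterns, in either direction: 0 v 5 events and 1 v 7 events.

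- 0 v 5: Fisher p = 2 x C(55,5) / C(110,5) = 2 x 3,478,761 / 122,391,522 = 0.057.
- 1 v 7: Fisher p = 2 x [C(55,8) + 55 x C(55,7)] / C(110,8) = 2 x 12,378,591,225 / 409,705,619,895 = 0.060.
- Boschloo's p-value is 0.045 for both.

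**Step 4: the gain at 2% v 10%.** It equals the probability of those two patterns; the reverse direction is negligible.

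- 0 v 5: 0.98^55 x C(55,5) x 0.1^5 x 0.9^50 = 0.329 x 0.179 = 0.059.
- 1 v 7: (55 x 0.02 x 0.98^54) x C(55,7) x 0.1^7 x 0.9^48 = 0.369 x 0.129 = 0.048.
- Sum: 0.107, or about 11 points.

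**Step 5: full enumeration at 55 per arm.** Chi-square is used unless an expected count is below 5, and the exact test otherwise.

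| Assumed rates | With Fisher | With Boschloo |
|---|---|---|
| 1% v 10% | 35% | 49% |
| 2% v 10% | 26% | 37% |
| 2% v 15% | 65% | 73% |
| 5% v 15% | 39% | 42% |
| 5% v 20% | 68% | 69% |
| 10% v 25% | 56% | 56% |

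In the last row sparse tables occur in only about 0.4% of trials, so the choice of exact test hardly matters.

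**Step 6: the primary endpoint.** Exact power at 96% v 77%:

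| Evaluable per arm | Chi-square | Fisher always | Fisher only if an expected count is below 5 |
|---|---|---|---|
| 49/49 | 85.0% | 72.5% | 82.6% |
| 50/50 | 85.1% | 73.8% | 83.7% |

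With 99 patients split unevenly, the last column is about 81-82%.

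**The case against.** **Fisher's test is valid, and the choice is one of taste.** It is valid and its conservatism is no error. That stands, and it is why the point is low in severity. Complications are also secondary and are reported as risk ratios with 95% confidence intervals, so the safety reading does not rest on a p-value alone.

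**The gain depends on rates the protocol does not give.** This also stands. Section 2.4.3 calls only serious complications and significant displacement rare. Nothing suggests that the skin reactions in section 9.2 are, and for common events there is no gain. A reader might infer a fixed loss of about 10 points. If the exact test were always used, the gap between Fisher and Boschloo would run from about 4 to 15 points at 49-50 per arm, depending on the rates, so no single figure can be stated as fact.

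**A reader might also infer that the primary comparison is underpowered**, setting Fisher's 72-74% at equal arms of 49 or 50 against the stated 80%. The document does not support this. Chi-square is a permitted test, it reproduces 110, and power stays at about 81-84% when Fisher is kept for sparse tables. The lower figure needs Fisher in every case, which the protocol does not say. Even then Fisher reaches 80.3% with 50 splint and 49 cast patients, and 79.5% if all 110 are evaluable.

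**The protocol does not say when Fisher replaces chi-square.** That detail is commonly left to the statistical analysis plan, which is not shown, so it is no finding here.

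**Conclusion.** A free improvement of low severity. For sparse two-by-two tables the protocol names a valid exact test where a more powerful one holds the same 5% limit and rejects whenever Fisher's test does. At 55 per arm, with the exact test used only when an expected count is below 5, the gain is about 8-14 points when the lower complication rate is 1-2%, 3 points or less at 5%, and none at 10% v 25%. These sizes rest on assumed complication rates and on an assumed rule for choosing the exact test.

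The primary sample size stands. It would also be a mistake to conclude that chi-square should be imposed on the primary endpoint with no exact fallback: its true error can reach about 6% at these sizes, which trades away error control instead of improving the plan at no cost.

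**What to change.** In sections 10.1 and 10.2, replace Fisher's exact test by Boschloo's exact unconditional test wherever a small-count comparison of two groups on a yes/no outcome is needed, complications above all. Keep the risk ratio and 95% confidence interval for complications. Fisher's test can remain for tables with more than two categories.

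The cost is a short wording change and a test that some readers will know less well; it is available in standard software. No extra patients, visits or data are needed, and section 5.3 does not change.
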